# Doll therapy intervention for women with dementia living in nursing homes: a randomized single-blind controlled trial protocol

**DOI:** 10.1186/s13063-020-4050-8

**Published:** 2020-02-03

**Keywords:** Doll therapy, Dementia, Behaviour, Caregivers, Attachment

## Abstract

**Background:**

Doll therapy is a non-pharmacological intervention for people with dementia aimed to reduce distressing behaviours. Reliable results on the efficacy of Doll therapy for people with dementia are needed. The concept of attachment theorised by Bowlby has been proposed to explain the Doll therapy process, but it has not been proven to influence the response to doll presentation.

**Methods/design:**

This single-blind, randomised controlled trial will involve people with dementia living in nursing homes of the Canton Ticino (Switzerland). Participants will be randomised to one of two interventions: Doll Therapy Intervention or Sham Intervention with a non-anthropomorphic object, using a 1:1 allocation ratio. The two interventions will consist of 30 daily sessions lasting an hour at most, led by a trained nurse for an hour at most. We will enrol 64 participants per group, according to power analysis using an estimated medium effect size (*f* = 0.25), an alpha level of 0.05, and a power of 0.8. The primary goal is to test the efficacy of the Doll Therapy Intervention versus the Sham Intervention as the net change in the following measures from baseline to 30 days (blinded outcomes): the Neuropsychiatric Inventory-Nursing Home administered by a trained psychologist blinded to group assignment, the professional caregivers’ perceived stress scale of the Neuropsychiatric Inventory-Nursing Home, patients’ physiological indices of stress (salivary cortisol, blood pressure and heart rate) and interactive behaviours. The secondary goal is to assess the relationship between attachment styles of people with dementia (detected by means of the Adult Attachment Interview to the patients’ offspring) and their caregiving behaviours shown during the Doll Therapy Intervention.

**Discussion:**

This is the first single-blind, randomised controlled trial on the efficacy of Doll therapy for dementia and an explanatory model of the response of people with dementia to doll presentation.

**Trial registration:**

ClinicalTrials.gov, ID: NCT03224143. Retrospectively registered on 21 July 2017

## Background

Doll therapy (DT) is a non-pharmacological intervention to support people with dementia (PWD) and is recommended for the treatment of behavioural and psychological symptoms of dementia (BPSD) [1]. Previous literature provided some direction on how to use dolls as a nursing instrument [2–6]. Observational studies have shown the benefits of DT in reducing BPSD such as agitation, aggression and wandering [7, 8]. They have also shown the benefits of DTS in increasing communication between patients and caregivers due to the fact that dolls stimulate conversation on topics related to motherhood and caregiving [9, 10]. A significant reduction of antipsychotic drug dosage (e.g. haloperidol) has also been reported [11]. Furthermore, the benefits provided from DT fulfil the bioethics’ concepts of beneficence (facilitates the promotion of well-being) and respect for autonomy (PWD can exercise their right to engage with dolls if they wish) [12]. Despite promising results, available studies on the efficacy of dolls’ use are mainly pilot or exploratory studies [13–15]. Randomised controlled trials are needed in order to support the clinical efficacy of DT in managing BPSD and reducing professional caregivers’ perceived stress linked to BPSD. Moreover, empirical research is needed to identify best practice for DT interventions for PWD because there are differences among approaches to the practice being advocated. There are also difficulties in standardising the design and delivery of such complex interventions [16].

Another issue is the explanatory model of the DT process. Some authors have applied the concept of attachment theorised by John Bowlby to the ‘doll’ object [15, 17]. Attachment theory holds that the propensity of human beings to seek closeness and protection when feeling vulnerable or frightened is an expression of an innate motivational system. This system activates attachment behaviours directed to achieve proximity and protection from another person (i.e. crying, calling, approaching and holding). The attachment behaviours persist during the entire life cycle, ‘from the cradle to the grave’ [18], and are linked to three types of mental states: secure, insecure and unresolved [19]. This motivational system is particularly relevant for PWD, since dementia often exposes them to feelings of personal vulnerability [20, 21]. The observation of DT interventions revealed that PWD recognised the doll as a real baby and replaced the requests for care and protection (through attachment behaviours, i.e. vocalisations, gestures and tears) with caregiving behaviours (i.e. reassuring and cradling the doll and restoring a sense of calm and peacefulness). The attachment theory could frame the therapeutic function of the doll for PWD in the advanced stages. Such an explanatory model of the DT process has been proposed in a previous study [15], but more robust empirical research is needed in order to confirm it.

In the present single-blind, randomised controlled trial, the first hypothesis regards the 30-day efficacy of the DT on BPSD, professional caregivers’ perceived stress linked to BPSD, patients’ physiological indices of stress, and interactive behaviours. The second hypothesis is that the past attachment styles, embedded during one’s life cycle, are stable even in the advanced stages of dementia. It is also hypothesised that the caregiving behaviours of PWD shown during the doll presentation are linked to their attachment styles.

## Methods/design

### Primary goal

The primary goal of the present study is the 30-day efficacy of the Doll Therapy Intervention (DTI) versus a Sham Intervention (SI) on BPSD, professional caregivers’ perceived stress, patients’ physiological indices of stress, and interactive behaviours of PWD living in a nursing home. In particular, we expect an improvement in terms of a decrease in the Italian version of the Neuropsychiatric Inventory-Nursing Home total score (NPI-NH) [22, 23]. We also expect an improvement of professional caregivers’ perceived stress linked to BPSD of PWD in terms of a decrease in the NPI-NH Distress (NPI-NH-D) total score. Furthermore, we expect an improvement of the patients’ physiological indices of stress linked to their BPSD in terms of a decrease in the following parameters: salivary cortisol, blood pressure (systolic and diastolic) and heart rate, which are well-known biomarkers of acute stress. Finally, we expect an improvement of the patients’ interactive behaviours towards the object (doll) in terms of an increase in the number and duration of exploratory and caregiving behaviours.

### Secondary goal

The secondary goal is the confirmation of the hypothesised stability of the past attachment style of the PWD (provided by the Adult Attachment Interview (AAI) [24] administered to the patients’ offspring (family caregivers), even in the advanced stages of dementia. The current attachment style of the PWD is provided by the observations of the patient during a situation of meeting-separation from their own family caregiver. These evaluations will be conducted, after conclusion of interventions, among a sub-group of participants in the experimental condition. We expect to find an association between the past and the current attachment style of the PWD, categorised as secure, insecure, and unresolved. Furthermore, the relationship between patients’ attachment styles and the response to DTI in terms of caregiving behaviours towards the doll (e.g. caressing the object, talking to it and smiling) will be investigated. We expect that PWD with a previous secure attachment style will accept the doll and will show more caregiving behaviours compared to PWD with insecure attachment style, while these latter will show more rejection, avoidance or excessive caregiving reactions towards the doll. We also expect that PWD with unresolved attachment style will show inconsistent responses to the doll presentation, with approaching and rejecting behaviours.

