### Sample size

To our knowledge, at the start of the study on 1 February 2017, no previous study had measured the efficacy of DT using the NPI-NH score. Therefore, a referral upon existing data could not be used in the power calculation. The power analysis was conducted using an estimated medium effect size (*f* = 0.25), an alpha level of 0.05, and a power of 0.8. According to statistical computing, a sample size of *n* = 128 is required, with 64 participants per group, for an analysis of covariance that includes the NPI-NH baseline score as a covariate. We planned an increase in sample size of 13 participants, because the expected drop-out rate is 10% due to possible acute clinical conditions interfering with the participation in the study, or death. In case of a refusal of the object (doll or cube), another participant will be enrolled as a replacement. Participants who underwent less than 60% of sessions will be excluded from analysis. The power calculation was performed with the programme *G*Power* 3.1 [27].

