### Secondary outcomes

#### Confirmation of stability of attachment style

Assessment of premorbid attachment style of PWD (Adult Attachment Interview (AAI)).

We have planned to study 30 patient-offspring couples (about 47% of the participants in the experimental group). When offspring who regularly visit the patient have accepted the interview, the AAI will be administered to a son or daughter of a patient among those in the DTI group. The AAI is a semi-structured interview designed to evaluate attachment styles in adult populations and allows us to identify three different categories of mental states related to the attachment style of the son or daughter of the PWD: free, dismissing/preoccupied, or unresolved. Free adults have positive internal representations about past relationships with their parents and feel free to explore their infant experience. Dismissing or preoccupied adults (categorised as insecure attachment) fail in telling coherent attachment stories about their parents; they are inclined to idealise or denigrate the role of their parents in the past. Unresolved adults show problems with past mourning experiences and unresolved trauma occurring during infancy. Since a correspondence of 75% between the individual’s attachment and that of their children has been reported [33], we can hypothesise that the AAI is a useful instrument to infer the premorbid attachment style of PWD. This semi-structured interview will be administered in the nursing home and will be video-recorded. The coding of the answers will be carried out by an external trained and authorised psychologist.

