### Statistical analyses

As a first step, a post hoc evaluation by descriptive statistical comparisons between the intervention and the control groups in age and baseline NPI-NH will be conducted to assess the effectiveness of the randomised assignment. To evaluate associations between biological parameters (decreased, influent, or increased) of each patient at the baseline versus the post intervention, the chi-square test or Fisher’s exact test will be performed. Primary outcomes will be tested performing an analysis of covariance (ANCOVA) of these measurements with the experimental group as the factor baseline NPI-NH and total number and posology of psychopharmacological therapies as the covariates. In order to evaluate how much variance in NPI-NH net change can be explained by groups (experimental versus control groups) after controlling for baseline NPI-NH and biological parameters, a multiple regression analysis will be performed.

Treatment efficacy will be analysed by a per-protocol analysis (PPA) that excludes all drop-outs. Differences will be considered statistically significant when *p* values are lower than 0.05.

All analyses will be conducted using Stata version 13 (Stata Corp., College Station, TX, USA).

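### Replacing residents who refuse the doll, then drawing the attachment pairs from the doll arm after the interventions, truncates the acceptance-versus-refusal part of the attachment hypothesis

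*Protocol article*

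**What the plan says.** All references are to the Protocol article.

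- **Predictions (Secondary goal).** The protocol expects that "PWD with a previous secure attachment style will accept the doll" and show more caregiving behaviour than insecure residents. Of insecure residents it says "these latter will show more rejection, avoidance or excessive caregiving reactions towards the doll". For the unresolved style it expects "inconsistent responses to the doll presentation, with approaching and rejecting behaviours".
- **Handling of refusal (Sample size).** "In case of a refusal of the object (doll or cube), another participant will be enrolled as a replacement". The same section adds: "Participants who underwent less than 60% of sessions will be excluded from analysis".
- **Source and timing of the pairs.** Secondary goal: "These evaluations will be conducted, after conclusion of interventions, among a sub-group of participants in the experimental condition". Confirmation of stability of attachment style: "We have planned to study 30 patient-offspring couples (about 47% of the participants in the experimental group". That section also requires offspring who visit regularly and accept the interview.
- **Recording of the response.** Table 1, item 1.b, has rows for acceptance, refusal and avoidance of contact. It is completed from video of the first and the 30th session.
- **Analysis.** Assessment of current attachment style of the PWD expects a correlation between attachment style and response to the doll intervention.

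**The concern.** Whether the resident takes or rejects the doll is one of the responses that attachment style is supposed to predict. If residents who reject it leave the sample before attachment is assessed, the sub-study conditions on part of its own outcome. If the hypothesis is true, the loss falls mostly on the styles predicted to reject. The design would then work against the hypothesis it is meant to test.

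The Discussion part of the abstract presents an explanatory model of the response to the doll as a contribution of the trial. A weak or absent association on acceptance could reflect the sampling, and later analysis could not repair this, because interviews never offered to the offspring of refusers cannot be recovered. The efficacy comparison is a separate matter and is not at issue here.

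**Working it through.** **1. The plan's own figure.** 30 pairs / 64 participants in the doll arm = 46.9%, which matches the stated figure of about 47%. The base is the planned 64, the number that replacement is meant to maintain. It is not everyone randomised to the doll.

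**2. The rules in sequence.**

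| Step | Section | Consequence |
|---|---|---|
| Doll offered; refusal possible | Description of interventions, Table 1 | Refusal is a recordable response |
| Refuser replaced | Sample size | The replacement takes the refuser's place among the 64 |
| Under 60% of sessions: out of analysis | Sample size | Possible second filter on residents who keep rejecting |
| Pairs taken from the doll arm after the interventions | Secondary goal | Drawn from those who remain |

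No section keeps replaced refusers for the attachment analysis, and none assesses attachment before the doll is offered. For the refusal that triggers replacement, the sub-group therefore has no variation, and that refusal cannot correlate with style.

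**3. Illustration.** The protocol gives neither refusal rates by style nor a style distribution. Everything below is assumed: 15 secure and 15 insecure residents, with refusal probabilities *s* (secure) and *i* (insecure). The unresolved style is left out for simplicity.

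- Expected refusers among 30 if nobody is removed = 15 × (*s* + *i*)
- Insecure share after removal = (1 − *i*) / [(1 − *s*) + (1 − *i*)]

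| *s* / *i* | Difference in refusal, all kept | Expected refusers | Insecure share after removal (from 50%) |
|---|---|---|---|
| 5% / 20% | 15 points | 3.75 | 0.80/1.75 = 46% |
| 10% / 40% | 30 points | 7.5 | 0.60/1.50 = 40% |
| 20% / 60% | 40 points | 12 | 0.40/1.20 = 33% |
| 10% / 60% | 50 points | 10.5 | 0.40/1.30 = 31% |

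**4. Effect on the negative responses that remain.** Suppose refusal is 10% / 40% and avoidance without refusal is 10% / 20% (secure / insecure).

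- All kept: (40% + 20%) − (10% + 10%) = 40 points.
- Refusers removed: 0.20/0.60 − 0.10/0.90 = 33.3% − 11.1% = 22 points.
- Power at 15 versus 15 (normal approximation, two-sided 5%) falls from 0.62 to 0.30.

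If avoidance is 10% in both styles, the difference falls from 30 points to 0.10/0.60 − 0.10/0.90 = 6 points, and power from 0.40 to 0.06.

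**The case against.** **The response of interest is mainly caregiving behaviour.** Secondary goal names caregiving behaviours towards the doll, and Table 1 item 3.b records their presence, type and duration. All of this can be seen in residents who take the doll, and excessive caregiving can be seen only in them. This stands, and it limits the point to acceptance versus refusal and to the style mix of the sub-group.

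**Exclusion of refusers is not written outright.** The replacement sentence sits in the sample-size section. The pairs come from participants in the experimental condition, with no explicit restriction to acceptors or completers. The per-protocol rule is stated for efficacy only: "Treatment efficacy will be analysed by a per-protocol analysis (PPA) that excludes all drop-outs". This also stands. The exclusion is an inference from replacement plus sampling after the interventions, though a strong one, and nothing in the text points the other way.

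**A reader might infer that refusal must be zero in both styles, or that the predicted response vanishes altogether.** The text does not support that. It does not say which session's refusal triggers replacement. A resident who accepts at first and refuses later, even at session 30, could remain with that refusal recorded.

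**A reader might also infer that any null result would be a sampling artefact.** That does not follow. With 30 pairs, and premorbid style inferred through a reported 75% parent-child correspondence, a null result has other plausible explanations.

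**The stability goal does not depend on doll acceptance.** Correct: it compares past with current style. Only the mix of styles in its sample may shift.

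**Conclusion.** The concern holds in a limited form and is worth correcting. As written, the plan selects the attachment sub-group on part of the response to be explained. The acceptance-versus-refusal component is truncated, and the sub-group may be depleted of the insecure and, in part, the unresolved styles. The rest of the attachment-response hypothesis remains testable.

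The conclusion rests on reading replacement as removal from the group from which pairs are later drawn. Its direction follows from the protocol's own predictions, but its size is unknown. In the assumed scenarios the insecure share falls from 50% to between 46% and 31%, and the difference in any negative response shrinks from 40 to 22 points or from 30 to 6. These figures show the mechanism and are not estimates for this trial.

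Removing the bias would not make the sub-study well powered. With all refusers kept, exact power for the refusal difference at 15 versus 15 (Fisher's test) ranges from 0.08 to 0.74 over the four assumed rate pairs.

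**What to change.** 1. State that all residents randomised to the doll arm are eligible for the 30 pairs, including those who refused and were replaced, subject to the existing conditions on offspring visits and acceptance of the interview.
2. Offer the interview and the family visit regardless of acceptance of the doll or completion of the sessions.
3. Define the refusal that leads to replacement, including the session to which it applies, and count refusal at the first session as a response category in the attachment-response analysis. First sessions of all participants are already videotaped.
4. Report how many doll-arm residents were replaced for refusing.

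**Cost.** The number of pairs and interviews stays at 30. Some pairs will have no session-30 video, and replaced refusers need a set time for the visit and continued contact until then. Selection through offspring who visit and agree to be interviewed remains. Trial status describes recruitment as ongoing with completion expected in February 2020, so for residents already replaced the change depends on whether their families can still be approached.

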### Ethical considerations

The study procedures are in accordance with the principles outlined in the Declaration of Helsinki of 1964 and the following amendments. The study protocol was submitted to, and approved by, the Swiss Ethics Committees on Research Involving Humans (Ref. no. CE3140 BASEC2016–01992). The recruitment phase is ongoing. Briefly, during recruitment of the participants we check the presence of the aforementioned inclusion and exclusion criteria in order to establish the eligibility of each patient. Then, the patients or their legal representative (families) will be asked to sign a written informed consent for the use of their personal data and will receive a concise and comprehensive briefing explaining the research objectives and methods of data processing.

### Study design

This study is a single-blind, randomised controlled trial with two parallel arms, conceived to assess the 30-day efficacy of the DTI compared to SI with a non-anthropomorphic object in PWD living in nursing homes (Fig. 1). The study is conducted and reported in accordance with the Consolidated Standards of Reporting Trials (CONSORT) guidelines for non-pharmacologic treatments [25] and with the SPIRIT (Standard protocol Items: Recommendations for Interventional Trials) guidelines (see Additional file 1). Principles of the Medical Research Council (MRC) Framework have inspired us in order to develop the DTI, to standardise the experimental and SIs, to set up procedures for monitoring delivery of the intervention, to evaluate the interventions and describe in depth all the procedures to enable replication studies [16]. The study is part of a larger project focussing on DT dissemination in Canton Ticino (Switzerland) through team training and supervision and guidelines‘ definition that led to the establishment of the Ticino Doll Therapy Group with support of the Canton Office for Elderly and Home Care. The phases of the project are as follows:
A first phase aimed to inform all nursing home operators and patients’ relatives about the establishment of a training programme on DT that they can join if interestedAn ad hoc training phase addressed to professional operators. Nursing assistants are trained to use dolls and to record responses through appropriate daily gridsThe research phase, described below, that will take place at the end of the informative and training phase

**Fig. 1 Fig1:**
[figure not shown]
Trial flow chart

### Participants and setting

Participants will be PWD living in 22 nursing homes of the Canton Ticino area, Switzerland. Participants will meet the following inclusion criteria: presence of moderate to severe dementia, assessed using the Global Deterioration Scale (GDS 4–7) [26]; presence of at least one BPSD in addition to depression or apathy assessed with the NPI-NH; female gender; admission in the nursing home at least 3 months before; and no previous DT exposure. The exclusion criteria were the following: male gender; presence of comorbid mental disorders, such as major depression, bipolar disorders and schizophrenia; inability to sit comfortably on a chair or limitations in mobility of the arms; or presence of acute clinical conditions interfering with the participation to the study.

